# Study protocol for a zinc intervention in the elderly for prevention of pneumonia, a randomized, placebo-controlled, double-blind clinical pilot trial

**DOI:** 10.3389/fnut.2024.1356594

**Published:** 2024-02-21

**Keywords:** zinc, pneumonia, intracellular immune cell zinc, older adults, nursing home residents, immunity, study protocol, COVID-19

## Abstract

**Clinical trial registration:**

https://clinicaltrials.gov/, NCT05527899.

## Introduction

1

Pneumonia (PNA) poses a significant public health challenge, particularly for older individuals residing in nursing homes (NH) (1). In comparison to independently living older adults, NH residents have a higher frequency of infections, with PNA being the leading cause of infection-related hospitalization (2–4). Recent data points to a concerning trend of increasing incidence and mortality from PNA in older individuals (5). The annual incidence of PNA for older adults (>65 y) residing in the community is estimated at between 25 and 44 per 1,000 persons (4), whereas in long-term care facilities the incidence ranges from 99 to 912 episodes per 1,000 persons, with a median of 365 per 1,000 persons, a tenfold difference in incidence (1). When combined with influenza, PNA becomes the 5th leading cause of death in elderly individuals aged 65 to 74 y and the death rate from these infections increases exponentially above the age of 55 y (3). The economic impact of PNA is high, with treatment costs of $480/case in NH, and the cost for hospitalization exceeding $7,000/case (6). Therefore, it is imperative to implement effective strategies to prevent PNA in older adults.

One important contributing factor to the higher incidence of PNA in older adults is the age-associated decline in T cell function and the naïve T cell pool (7, 8). Intriguingly, there are striking similarities between zinc (Zn) deficiency and age-induced immunological changes (9, 10). In both cases, T cell defects have been identified as key contributors to higher susceptibility, morbidity, and mortality from infectious diseases, including PNA (9, 11–16). Previously, we reported that that 29% of NH residents in and around the Boston area had low serum Zn levels (<70 mg/dL), which was associated with significantly higher incidence and duration of PNA, increased antibiotic use, and overall mortality (17). Importantly, these associations were independent of age, BMI, albumin levels, other micronutrient levels, C-reactive protein (CRP), and other predisposing diseases for PNA.

Many studies have demonstrated that Zn supplementation enhances T cell-mediated function in Zn-deficient individuals, such as the elderly. Preliminary findings from our randomized, double-blind, placebo-controlled trial revealed that supplementation of elderly individuals with low serum Zn levels with 30 mg/d of Zn gluconate for 3 months improved serum Zn levels in majority but not all of the older adults (18). Specifically, 42% of those who completed the study in the Zn group did not reach adequate serum Zn concentrations (≥70 μg/dL) by month 3; these participants had very low serum Zn levels at baseline, with a mean ± SD of 53 ± 6 μg/dL and a range of 44–60 μg/d. Adjustment to increased Zn intake in highly Zn-deficient participants may require higher level of Zn supplementation or longer than 3 month supplementation period. Regardless, in this study we observed on average a significant increase in the percent of CD4+ T cells, and better maintained T cell function. A significant correlation between serum Zn level and T cell function, as assessed by their ability to proliferate, was also observed.

While our observational findings are supported by a small study conducted by Prasad et al. in which older adults supplemented with 45 mg/d of Zn for 12 months exhibited lower incidence of all infections including RI (19), there is an urgent need to demonstrate the efficacy of supplemental Zn to prevent pneumonia in older adults through a prospective clinical trial of adequate size and duration. As the first step toward that goal, we are conducting a 1-year double blind, placebo-controlled study to determine the effective and safe Zn supplementation dosage for NH residents. This dose will subsequently be used in a larger clinical trial to determine the effect of Zn supplementation in elderly NH patients with low serum Zn levels on the incidence of and morbidity from PNA. Additionally, results from a recent meta-analysis (20) indicated that Zn supplementation reduces the length of hospitalization in children with respiratory diseases. This further underscores the potential impact of Zn on respiratory health across different age groups.

Furthermore, while serum Zn levels serve as a reliable marker of Zn status at the population level and have been demonstrative to be responsive to supplementation, there is controversy about their accuracy in reflecting cellular Zn levels, which are important for optimal immune cell function, at the individual level. Since intracellular Zn levels are higher than serum levels, it is plausible that the serum Zn level may give an incomplete picture of cellular Zn state of an individual. Consequently, even in the presence of cellular Zn deficiency, serum Zn levels might fall within the lower end of the normal range. Therefore, as part of our primary objective, this pilot study will also evaluate how well serum Zn levels reflect cellular labile Zn levels prior to- and post-Zn supplementation. The findings of this proposal are scientifically essential, yet also sufficient, to make definitive decisions that inform the final design of our planned clinical trial.

## Methods and analysis

2

### Design

2.1

We are conducting a one-year long RCT to determine an effective and safe Zn supplementation dosage for elderly NH residents with low serum Zn levels (< 70 μg/dL), this threshold is recommended by Institute of Medicine, Panel on micronutrients (21) and others (22). Two Zn dosages, 30 or 60 mg/d, will be tested. The primary objectives are to establish the optimal dose of Zn supplementation required to achieve adequate serum Zn levels and estimate the correlation between serum and intracellular labile Zn levels. The secondary objectives are to assess adverse events and immune outcomes and collect data on PNA to design a larger clinical trial effectively. The selection of the dose will be determined by the combination of time and dosage that exceeds threshold for achieving adequate serum Zn levels in the majority of subjects (>90%) while remains below designated threshold for incidence of the side effects (<10% moderate or severe side effects, see below).

A total of 105 male and female elderly subjects (≥65 y) with low serum Zn (<70 μg/dL) will be enrolled from a NH within 1 h driving distance from Boston (from an estimated 16 NHs, ~900 residents) and be assigned to one of the 3 groups. Group 1 will serve as control and will receive a capsule containing ½ Recommended Dietary Allowance (RDA) of all the essential micronutrients (MN), including 5 mg of elemental Zn (1/2 RDA MN); group 2 will receive a capsule containing ½ RDA MN including 30 mg/d elemental Zn, and group 3 will receive a capsule containing ½ RDA MN including 60 mg/d elemental Zn. Zn is provided as Zn gluconate. The overall study design and number of subjects is shown in Figure 1 and the frequency of data collection is shown in Table 1.

**Figure 1 fig1:**
[figure not shown]
Zinc intervention in the elderly for prevention of pneumonia study flow diagram.

**Table 1 tab1:** Zinc intervention in the elderly for prevention of pneumonia study outcomes and collection frequency.

	Age	Sex	Race	Ethnicity	SES^1^	Supplement use (Ca, Vit D, Fe)	Smoking status	Alcohol status	Disease status	Prescribed medication	Serum & intra-cellular Zn	T cell profile	Cu, Fe, Ferritin, CBC^2^, albumin, CRP^3^, BMI^4^
Baseline	x	x	x	x	x	x	x	x	x	x	x	x	x
Month 4											x	x	x
Month 8											x	x	x
Month 12											x	x	x

^1^SES, Socioeconomic status. ^2^CBC, Complete blood count with differential. ^3^CRP, C-reactive protein. ^4^BMI, Body mass index. Total blood collected 120 mL. Other outcomes: Every 2 weeks: adverse event assessment- screen and record NH residents every 2 weeks for the following symptoms: nausea, vomiting, abdominal discomfort, neurologic abnormalities. Throughout the study: new disease, medications, transfers.

We will use each NH unit’s dose dispensing system to deliver the capsules as in our previous NH Study (23). In that study, 98% of subjects consumed the capsule for more than 90% of the 1-y supplementation period. Adherence will be checked by measurement of Zn from blood samples collected every 4 months (Table 1).

### Study population and eligibility criteria

2.2

Study participants will be long-stay elderly NH residents (≥65 y). Long-stay residents of NH are at high risk of PNA and have higher morbidity and mortality due to PNA (3). Our previous study showed that Zn deficiency is prevalent in NH residents (29%), and those with low Zn had higher incidence and morbidity from PNA (17). In addition, the need for a year-long study to capture seasonal variation in infection, for careful documentation of infections, and to keep as many as dietary and environmental factors constant in our future randomized clinical trial, makes the NH setting preferable.

#### Inclusion criteria

2.2.1

The inclusion criteria for this study are: older individuals (≥ 65 y), with a > 6-month life expectancy (as judged by the physician), who are willing to be randomized into the 3 study groups, can swallow pills, are not currently on antibiotics, willing to receive influenza vaccine, and have a BMI > 18 kg/m^2^ and albumin >3.0 g/dL (Table 2). If participant is consuming RDA levels of supplement, they must be willing to replace their supplement with our control supplement. Calcium, vitamin D, and iron supplements are permitted.

**Table 2 tab2:** Exclusionary and inclusionary criteria.

Inclusion criteria	Exclusion criteria
Elderly males and females (>65 years) >6-month life expectancy, as judged by physician Willing to be randomized into study groups Able to swallow pills Not currently on antibiotics If consuming RDA levels of supplement, willing to replace with our control supplement; calcium, vitamin D and iron supplements are permitted Willing to receive influenza vaccine BMI > 18 kg/m ^2^ and albumin >3.0 g/dL	Anticipated transfer or discharge within 3 months of enrollment Bed- or room-bound continuously for previous 3 months Presence of lung neoplastic diseases or other neoplastic diseases requiring chemotherapy and/or immunosuppressive drugs (including ≤10 mg/day prednisone) Nasogastric or other tube feeding Long-term (≥30 days) IV or urethral catheters Presence of tracheostomy or chronically ventilator-dependent Chronic prophylactic antibiotic treatment or long-term antibiotics Those with PEM defined as albumin <3.0 g/dL and BMI <18 kg/m^2^ Consumption of supplements containing more than the RDA level of nutrients known to affect the immune response, i.e., vitamins E, C, B6, selenium, Zn, or β-carotene Diagnosis of PNA or other infection at baseline will not exclude a subject, but will postpone enrollment to 4 wks after PNA symptoms have cleared

### Intervention

2.3

We are conducting a randomized, double-blind, and placebo-controlled trial, in which Zn deficient NH elderly (< 70 μg/dL) will be supplemented with a control (½ RDA of all micronutrients including 5 mg/d of Zn) or ½ RDA of micronutrients with total of 30 or 60 mg/ of elemental Zn for 12 months.

### Outcomes

2.4

#### Primary outcomes

2.4.1

The primary outcomes of this study are twofold: to identify an effective and safe Zn supplementation dosage for NH residents as well as to investigate the correlation between serum and cellular T cell or neutrophil Zn levels. Blood will be collected using appropriate Zn-free syringes, gloves, and tubes. Serum Zn concentration will be measured as described (24, 25). To quantify labile Zn in neutrophils RBC’s will initially be removed from whole blood using an RBC lysis buffer (eBioscience) compatible with flow cytometric analysis and minimally impacting lymphocytes. For assessment of labile Zn in pan-T cells, PBMC’s will be isolated using SepMate PBMC isolation tubes following the manufacturer’s instructions. Labile Zn in both pan-T cells and neutrophils will be determined as previously reported (26). Briefly, each resulting cell suspension, containing an estimated 2 × 10^6^ cells, will be loaded with 1 μM FluoZin3-AM ester and incubated with 2 μM N, N, N′, N′- tetrakis-(2 pyridylmethyl) ethylenediamine (TPEN, for minimum value or F_min_) or 100 μM Zn sulfate and 50 μM pyrithione (for maximum value or F_max_). The cells will then be stained with fluorescence labeled anti-CD3 (T cells) or anti-CD16b (neutrophil) antibody. Pan-T cells will be analyzed in a flow cytometer for the fluorescence intensity of FluoZin-3 in FL-1 and anti-CD3 in FL-4, while neutrophils will undergo flow cytometric analysis for fluorescence intensity of FluoZin-3 in FL-1 and anti-CD16b in the FL-4 channel.

While the study is not powered to determine incidence of PNA, we will document PNA incidence to gain insight into any logistical issues and, if needed, adjust sample size for the clinical trial. We will diagnose PNA using criteria established by the Infectious Diseases Society of America/American Thoracic Society IDSA/ATS on community acquired pneumonias (27). In this pilot trial sputum cultures and chest X rays will only be obtained by the discretion of the care-taking doctor. The study physicians will collect data from the subject examinations, interviews, and record reviews to determine incidence and duration of PNA. Symptoms can include cough with or without sputum production, chest pain, dyspnea, and fever. Signs of infection include elevated temperature (≥38°C), tachycardia, tachypnea, abnormal breath sounds, and dullness to percussion of the chest. The diagnosis requires radiological findings of 1 or more new pulmonary infiltrates. An infection is considered resolved when all symptoms cease. A new infection is defined as one occurring after ≥7 symptom-free days. These procedures were successfully used in our previous study (17). We will visit each individual NH routinely every 2 weeks and perform a chart review and a focused physical exam (lung for PNA and GI, for adverse events) on all study participants. While not a secondary outcome of the study, upper and other lower RIs will be documented using procedures described before (17).

We will screen and record NH residents every 2 weeks for the following symptoms/adverse events: (1) Minor side effects: Nausea, and bad taste. These side effects were relatively common in studies using doses well above 60 mg/day. If patients are willing to continue taking Zn despite these minor side effects, we will continue Zn supplementation. (2) Moderate side effects: Nausea, vomiting, stomach pain, diarrhea. These adverse events are extremely rare at doses of 30 and 60 mg/day. These will be designated as not acceptable, and participants will be dropped from the study. (3) Severe side effects: Flu-like symptoms (fever, chills, cough, headache), neurologic symptoms such as paresthesia, gait disturbance or photophobia. These adverse events have not been reported at doses of 30 and 60 mg/d. Participants exhibiting these adverse events will be dropped from the study. We will record the number of side effects and their duration throughout the 12-months duration of the study for both Zn doses. If treatment stops due to adverse events this event will be counted as such, and participant will be dropped from study. If at any point more than 10% of planned enrollments have experienced at least 1 moderate or severe side effect, we will close this study arm.

Clinical chemistry profile, albumin, Cu, Fe, Ferritin, CRP, and complete blood count with differential measures (CBC-diff) will be analyzed on all subjects as previously described in our Zn supplementation study (17, 18). Importantly, intestinal absorption of Cu is inhibited by Zn. Thus, chronic intake of high doses of Zn may be associated with Cu deficiency (28). This concern is the main basis for the upper tolerable limit (UL) for Zn (21). However, notably, this UL refers to chronic intake of Zn in subjects with adequate Zn level and does not preclude the use of higher doses of Zn for treatment of deficiency or diarrhea. The presence of 0.8 mg Cu in our placebo and Zn capsules will ensure no adverse effect on Cu status. Further, no serious adverse effects have been reported for long-term (up to 5 yrs) intake of up to 80 mg of Zn/day in older adults (29), who had baseline serum levels higher than those proposed in this study. Blood will be examined with a Baker 9,000 Hematology Analyzer for RBC and WBC counts and a blood smear will be used to estimate WBC differentials. This information will be used for statistical adjustment by analysis of co-variance and/or for assessment of side effects. CRP is included as it is a marker of inflammation which may impact Zn levels transiently and will be used for statistical adjustments as needed. BMI will be calculated from baseline weight and standing or knee height (in subjects who cannot stand or are contracted) (30).

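### The severe side-effect rule removes and counts anyone with fever, chills, cough or headache without an attribution rule, although cough and fever are also pneumonia symptoms to be followed; nausea sits in two tiers

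*Protocol article*

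**What the plan says.** Secondary outcomes (2.4.2) sorts side effects into three tiers.

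- **Minor:** nausea and bad taste. A willing participant may continue.
- **Moderate:** nausea again, with vomiting, stomach pain and diarrhea. The participant is dropped.
- **Severe:** "Severe side effects: Flu-like symptoms (fever, chills, cough, headache), neurologic symptoms such as paresthesia, gait disturbance or photophobia". The participant is dropped. The text adds: "These adverse events have not been reported at doses of 30 and 60 mg/d".

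An arm closes once more than 10% of planned enrolment has had at least one moderate or severe event. Design (2.1) and Statistical analysis (2.9) use a moderate or severe rate below 10% as the safety half of dose selection.

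The same section describes pneumonia, a secondary outcome covering incidence, duration, hospitalization and antibiotic use: "Symptoms can include cough with or without sputum production, chest pain, dyspnea, and fever". On follow-up it says: "An infection is considered resolved when all symptoms cease". A new episode counts after at least seven symptom-free days. Other respiratory infections are also recorded: "upper and other lower RIs will be documented using procedures described before". At the two-weekly visit, staff "perform a chart review and a focused physical exam (lung for PNA and GI, for adverse events) on all study participants". A pneumonia diagnosis needs a new infiltrate, but "chest X rays will only be obtained by the discretion of the care-taking doctor".

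The Table 1 footnote gives a shorter adverse-event list: "screen and record NH residents every 2 weeks for the following symptoms: nausea, vomiting, abdominal discomfort, neurologic abnormalities".

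**The concern.** Cough and fever have two roles in one section. As pneumonia symptoms they are to be followed until they resolve, with watch kept for recurrence. As severe side effects they end participation. The tier paragraph gives no rule for telling the two apart, and its trigger is that the participant shows the symptom, not that the supplement is suspected.

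Three things are at stake.

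- **Dose selection.** The 10% limit is the safety half of the pilot's main decision. If respiratory illness is scored as a side effect, a harmless dose can be rejected or its arm closed.
- **Pneumonia data.** Someone removed at the onset of fever or cough cannot contribute duration, later treatment or recurrence.
- **Nausea.** Two assessors can put the same complaint in tiers with opposite consequences, and only one tier counts toward the limit.

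**Working it through.** **Inputs.** 35 per group, 27 evaluable, 20% attrition (Sample size, 2.5). Limit of 10% (2.1, 2.4.2, 2.9). Pneumonia incidence in long-term care of 99 to 912 per 1,000, median 365 (Introduction). The share of infections that staff would score as side effects is not given, so it is varied.

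**The plan's own figure.** One-sided Fisher's exact test, 58% against 90%, alpha 0.05: power is 79.8% at 26 per group and 81.3% at 27. The stated 27 reproduces and is not in dispute.

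**The limit in whole participants.** 3/35 = 8.6% passes; 4/35 = 11.4% fails both the closure and the selection limit.

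**Background risk that makes a harmless arm fail.** Let p be the 12-month probability that a participant is scored for background illness. Solve P(X ≥ 4) for X ~ Binomial(35, p), then convert to a rate r = −ln(1 − p) and divide by the quoted incidence.

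| Chance of failing | p | r | Share of pneumonias at 0.365 | Share at 0.099 |
|---|---|---|---|---|
| 5% | 4.0% | 0.0408 | 11% | 41% |
| 10% | 5.1% | 0.0521 | 14% | 53% |
| 20% | 6.6% | 0.0686 | 19% | 69% |
| 50% | 10.4% | 0.1097 | 30% | not reached |

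**The other direction.** p = 1 − exp(−incidence × share scored), then P(X ≥ 4):

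| Share scored | p at 0.365 | P(fail) | p at 0.099 | P(fail) |
|---|---|---|---|---|
| All | 0.306 | 99.8% | 0.094 | 42% |
| Half | 0.167 | 86% | 0.048 | 9% |
| Quarter | 0.087 | 36% | 0.024 | 1% |
| Tenth | 0.036 | 4% | 0.010 | 0.04% |

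**Other reading of the denominator.** If planned enrolment means all 105, then 10% is 10.5 and closure needs 11 events. With 11 or more required among the 35 in one arm, full scoring gives 52% at the median and under 0.1% at the lowest incidence. Half scored at the median gives P(X ≥ 11 | 35, 0.167) = 2.3%. This reading affects closure only. The selection limit in 2.1 and 2.9 is not tied to planned enrolment and reads naturally as a rate per dose.

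**Removals.** Full scoring at the median would remove 35 × 0.306 = 10.7, leaving 24.3. The attrition allowance is 0.20 × 35 = 7.

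**The case against.** The best reply is that the text, read as a whole, already implies attribution. The tiers are headed as side effects. The remark that severe events are unreported at these doses is implausible for cough or headache of any cause, so it makes sense only for zinc-related events. The two-weekly exam assigns the lung to pneumonia and the gut to adverse events. Causality assessment and grading are also commonly left to a full protocol that an article condenses.

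Much of this stands as evidence of intent. It does not settle the rule. The same paragraph speaks of symptoms and adverse events, removes those who show them, and closes arms on the count; 2.9 also says adverse events. The article itself states the tiers, the removal rule and the limit, so the fault lies in what is stated. Attribution will also be hard at the bedside. A febrile cough without an X-ray cannot meet the pneumonia definition; it could be recorded as another respiratory infection, but it also matches the severe tier.

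Three stronger readings are tempting and not supported.

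- **An arm will almost certainly close on background pneumonia.** The 99.8% needs every pneumonia scored at the median rate and a denominator of 35. Full scoring was probably not intended. General long-term-care rates may also overstate risk after the exclusions in 2.2.2.
- **The trial falls below its 27.** Under 2.9, only those who stop before reaching adequate zinc leave the proportion, and adequacy counts at its first occurrence. Participants who reach it and are removed later still count, so 24.3 is not comparable with 27.
- **The Table 1 footnote contradicts the tiers.** It is a shorter list that also omits diarrhea and bad taste. It needs aligning but is not a conflict in itself.

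The harm to pneumonia data is modest too: the plan says the study is not powered for pneumonia and collects these data to plan the larger trial. Finally, removal on suspicion is a defensible caution in frail residents.

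**Conclusion.** The point holds as a defect of stated wording and should be fixed; confidence is medium. The rule that removes participants, closes arms and screens doses turns on symptoms without regard to cause, while the same section follows two of those symptoms as an outcome. The nausea duplication is plain on the page and needs no inference.

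The size depends on a share that the document does not give. At the median incidence, modest and inconsistent scoring is enough to matter: about one pneumonia in seven gives a harmless arm a 10% chance of failing. At the lowest incidence it takes about half. At a tenth scored, the risk is 4% or less. These figures assume annual rates, Poisson episodes, 35 per arm, no zinc effect and general long-term-care incidence. Other respiratory infections, gastrointestinal illness and unrelated headache or gait problems are left out and would raise the count.

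**What to change.** Amend the side-effect paragraph in 2.4.2:

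1. State that only moderate or severe events not explained by a diagnosed infection or other intercurrent illness, as judged by the blinded study physician, trigger removal and count toward the closure and selection limits. A general rule is better than a respiratory exemption, because gastroenteritis, other fevers and unrelated gait problems raise the same issue.
2. Record infections, with or without an X-ray, through the infection procedures in the same section.
3. List nausea once, or separate the tiers by a stated grade.
4. State the 10% denominator as 35 per arm.
5. Report moderate and severe rates in the control arm beside both zinc arms. The two-weekly exam already covers all participants.
6. Align the Table 1 footnote with the tiers.

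**Cost.** A few sentences, one footnote and small case report form edits, with no new visits or tests. The downside is that a true zinc reaction may occasionally be put down to illness, which slightly softens a cautious stopping rule. The control-arm comparison is a partial check on that.

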### Statistical analysis

2.9

This pilot study is a randomized dose-finding trial with the primary objective to establish optimal dose of Zn supplementation to achieve adequate serum Zn levels and estimate association between serum and cellular Zn levels. The effectiveness will be assessed based on the ability to increase serum Zn levels to adequate levels in the majority of participants (>90%) and in the shortest duration of supplementation and at the same time results in <10% of moderate or severe adverse events. Subjects will be deemed Zn adequate on the first occasion where their Zn serum level reaches ≥70 μg/dL. Subjects will not be included in the calculation of this proportion if they discontinue supplementation before reaching Zn-adequate status. Pearson correlation will be estimated between serum and cellular Zn levels. Violations of linearity will be assessed graphically, and sample product moment correlation method (34) will be used to produce two-sided confidence intervals for the estimated correlation. Analysis among dose groups will follow an intention-to-treat approach. Comparison of proportion of Zn adequate between dose groups will be tested using Fisher’s exact test with risk ratios at each time point. Continuous outcomes that have repeated measures taken at baseline, 4, 8, and 12 months will be analyzed with mixed effects linear regression which considers within-subject correlation of outcomes. We will assume linear time trends and test the dose effect by the treatment by time interaction term. Assumptions of normality and homoscedasticity will be evaluated in these models and appropriate variable transformations will be applied if needed. Age, sex, and NH site will be included in the models as covariates. A significance level of 0.05 will be used for each secondary outcome. To control for multiple testing across groups, the type I error will be reserved for the comparison between the placebo group and the selected Zn dose group. Summary statistics on any missing data will be reported, including types and patterns of missingness. Subjects with partial outcomes over time can be included in the model fit since the mixed-effects linear modeling framework allows inclusion of subjects having different numbers of repeated measures. Multiple imputation based on the multivariate normal model will be used in the case of missing covariates. Analysis will be performed using SAS (version 9.4; SAS Institute, Cary, NC).

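### A moderate or severe side effect ends study follow-up as well as the capsules, so recovery off zinc and all later outcome data are lost for the participants harmed

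*Protocol article*

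**What the plan says.** Section 2.4.2 (Secondary outcomes) of the protocol article gives the removal rule three times.

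- Moderate side effects: "These will be designated as not acceptable, and participants will be dropped from the study".
- Severe side effects: "Participants exhibiting these adverse events will be dropped from the study".
- Any treatment stop for an adverse event: "If treatment stops due to adverse events this event will be counted as such, and participant will be dropped from study".

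Minor side effects are handled differently: a participant willing to carry on stays on zinc. Stopping because of a minor effect would fall under the third sentence.

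The same section describes what is to be collected.

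- Side effects: "We will record the number of side effects and their duration throughout the 12-months duration of the study for both Zn doses".
- The two-weekly visit, at which staff "perform a chart review and a focused physical exam (lung for PNA and GI, for adverse events) on all study participants".
- Laboratory measures, including copper, iron and ferritin, of which it says that these and "complete blood count with differential measures (CBC-diff) will be analyzed on all subjects". Directly after the blood count methods it adds: "This information will be used for statistical adjustment by analysis of co-variance and/or for assessment of side effects".

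Section 2.9 (Statistical analysis) states: "Analysis among dose groups will follow an intention-to-treat approach". Table 1 schedules blood at baseline and at months 4, 8 and 12.

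**The concern.** Stopping the supplement protects the participant. Ending follow-up gives no further protection and discards information. The third sentence quoted above treats the two as separate steps and requires both, so the wording cannot be taken as loose language for stopping capsules.

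The pilot is meant to name a safe dose for a larger trial. For a participant whose event is still going on at removal, it could not show how long the event lasted, whether it cleared once zinc was stopped, or whether copper or blood counts changed afterwards. Section 2.4.2 itself names copper deficiency as the main reason for the upper limit on zinc intake. Later T-cell and pneumonia outcomes would also be missing, and missing because of a side effect. A dose with more such events would lose more data, which is the kind of loss that an intention-to-treat comparison is meant to avoid.

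**Working it through.** **The plan's own figure.** Section 2.5 asks for 27 evaluable per group to detect 58% versus 90% conversion with a one-sided Fisher's exact test, alpha 0.05 and 80% power. Exact enumeration gives 79.8% at 26 per group and 81.3% at 27, so 27 is reproduced. With 35 enrolled and 20% attrition, 35 × 0.8 = 28 remain, which covers it. The sample size is not in dispute.

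**What survives removal and what does not**

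| Item | After removal under the rule |
|---|---|
| The event itself | Counted; the under-10% criterion remains computable |
| Baseline and earlier draws | Kept |
| Duration of an event resolved before removal | Kept |
| Duration of an event still ongoing | Cut off |
| Recovery off zinc | Not observed |
| Later copper, blood count, iron and ferritin | Not collected |
| Later T-cell and pneumonia data | Not collected |

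**How many people.** Inputs: 35 per arm (Section 2.5) and closure of an arm when more than 10% of planned enrolment has had at least one moderate or severe effect (Section 2.4.2), read here per arm. 0.10 × 35 = 3.5, so 3 affected participants (3/35 = 8.6%) leave the arm open and the fourth (4/35 = 11.4%) closes it.

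**How many draws.** Scheduled post-baseline draws per arm: 35 × 3 = 105. A removed participant loses 3 draws if removed before month 4, 2 between months 4 and 8, and 1 between months 8 and 12. With 3 participants removed:

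- Minimum: 3 × 1 = 3 of 105 (2.9%).
- Maximum: 3 × 3 = 9 of 105 (8.6%).
- If event timing is uniform over the year (assumption): (3 + 2 + 1)/3 = 2 draws each, so 6 of 105 (5.7%). Mean follow-up lost is 26 weeks each, so 78 of 35 × 52 = 1,820 person-weeks (4.3%).

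**Dependence on the event rate.** The article gives no expected rate for this trial. For assumed true rates in an arm of 35:

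| Assumed rate | Expected number affected | Chance of 4 or more |
|---|---|---|
| 2% | 0.7 | 0.5% |
| 5% | 1.75 | 9.6% |
| 10% | 3.5 | 46.9% |
| 20% | 7 | 93.9% |

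**Effect on power.** With 28 per arm after other attrition, exact power is 81.0%. Losing 3 more from the 60 mg arm (28 versus 25) brings it to about 79%. Power is not where the harm lies.

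**Consistency with the rest of the plan.** Recording duration over the 12 months cannot be done for an ongoing event once the participant has left. Intention-to-treat needs outcomes on participants after they stop treatment, and the rule ends their collection. The statement that laboratory measures cover all subjects is a weaker conflict, because it can be read as merely introducing the assay panel.

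**The case against.** The best reply is that the end of follow-up is inferred. The sentence on recording duration comes straight after the moderate and severe rules and carries no exception, so it might be meant to follow those events to their end. An article may also leave an early-termination visit or safety follow-up to the full protocol. This does not carry the point. The article does not merely omit follow-up after a treatment stop; it states that the participant leaves, and nothing in it provides for later contact.

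A second reply is that the dose decision is largely untouched. The incidence criterion survives. Zinc adequacy is fixed at the first value of at least 70 μg/dL, and those who stop supplementation before that are excluded from the proportion by Section 2.9, so later bloods would not change it as defined. The secondary safety outcome is a count of events, and pneumonia is unpowered. All of this stands, and it limits the severity.

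Third, the numbers are small. Section 2.4.2 describes moderate events as extremely rare at these doses and severe ones as unreported. That is fair, and the figures above illustrate the loss without forecasting it. Nor is 3 per arm a strict ceiling, because someone who stops over a minor effect is also removed without counting towards closure.

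Fourth, two of the supporting conflicts are soft. The sentence on using blood information to assess side effects follows the blood count methods and need not extend to copper. The mixed model does keep participants with partial records. That uses the data already collected but does not replace what is never collected, and the missingness here follows harm.

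**Conclusion.** The concern holds and should be fixed. It does not invalidate the dose selection. As written, the rule ends outcome collection because of harm, contrary to the stated intention-to-treat approach and to the undertaking to record event duration over the year.

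The loss is 1 to 3 post-baseline draws per removed participant, plus their remaining two-weekly reviews and pneumonia follow-up. With 3 events in an arm this is 3 to 9 of 105 draws. That range rests on reading the closing rule per arm and on 3 qualifying events occurring; the 5.7% midpoint also assumes uniform timing. The conclusion that post-removal data are lost for those harmed depends on none of these assumptions.

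**What to change.** In Section 2.4.2, keep every rule for stopping capsules, but replace the removal wording in all three sentences with: *supplementation stops; the participant remains in the study unless consent is withdrawn.* Continue the two-weekly reviews, recording each event to resolution or month 12. Continue the scheduled month 4, 8 and 12 bloods and mark samples taken off supplement. Those samples belong in the intention-to-treat comparisons, and the marking lets them be identified in the serum–cellular zinc analysis.

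The cost is a short protocol amendment and 1 to 3 further draws per affected participant, at most 9 per arm with 3 events. The visits and blood schedule already exist and the sample size does not change. The real burden is continued blood sampling in frail residents who have just had an unacceptable event; they may decline it.
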